##### Data Collection

###### Quality of Life Assessment

Participants in the cohort study will complete the validated quality-of-life questionnaire before surgery and again at 12 months postoperatively.

###### Femininity Perception Assessment

Femininity will be assessed through both self-perception and third-party evaluation. Self-perceived femininity will be measured using the questionnaire responses regarding this matter.

To assess changes in third-party perception of femininity, a blind evaluation will be conducted using standardized frontal and lateral clinical photographs taken preoperatively and at least 12 months postoperatively. All images will be coded using an alphanumeric identifier (eg, FFS01, for “facial feminization surgery participant 01”), which will not be visible to evaluators. A control group of cisgender women will be included, using anonymized clinical photographs from the Maxillofacial Surgery Service at San Juan de Dios Hospital, authorized for academic and research purposes.

Forty undergraduate students from nonhealth-related fields (eg, arts, philosophy, architecture, and social sciences) at the University of Chile will serve as evaluators. Participants will be recruited through institutional emails and social media platforms.

Inclusion criteria require students to be aged more than 18 years, without training or experience in health, facial anatomy, or aesthetics. Exclusion applies to students with previous engagement with transgender individuals from the hospital’s gender program. Each student will provide informed consent. Evaluators will rate randomized images (including preoperative, postoperative, and control cases) using a 5-point Likert scale ranging from “feminine appearance” (1) to “non-feminine appearance” (5).

Four groups of 10 evaluators each will be formed, ensuring diversity in gender and age. Each group will be randomly assigned a set of photographs, including preoperative, postoperative, and control images, all displayed in a randomized sequence. As a critical methodological safeguard, pre- and postoperative images of the same patient will not be included within the same group to minimize direct comparative bias.

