##### Sample Size Calculation for Cohort Study

The gender program at San Juan de Dios Hospital currently includes 70 transgender women undergoing hormone therapy and attending regular medical follow-up appointments. On the basis of this population size, a sample of 30 participants was calculated using a 95% confidence level and an estimated margin of error of 12%. This adjustment reflects logistical and ethical considerations related to long-term follow-up while maintaining sufficient statistical validity for exploratory analyses of surgical outcomes.

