##### Data Analysis for the Cohort Study

Descriptive statistics will be used to summarize sociodemographic variables (absolute and relative frequencies). The Shapiro-Wilk test will assess the distribution of continuous variables. Normally distributed variables will be reported as mean and SD; nonnormally distributed variables will be reported as median and IQR. Pre- and postoperative comparisons of continuous variables will be made using paired *t* tests or Wilcoxon signed-rank tests, as appropriate. Categorical variables will be compared using Pearson chi-square or Fisher exact test. Linear regression models will evaluate the associations between cephalometric and photometric changes and perceived femininity scores. Statistical significance will be set at *P*≤.05. All analyses will be conducted using Stata (version 11; StataCorp).

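### Pre and post photographs are rated by different student groups, so group severity adds unmodelled noise to each third-party femininity change; counterbalancing and a group term recover the lost precision cheaply.

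*Protocol article*

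**What the plan says.** Under Femininity Perception Assessment, the raters are "Forty undergraduate students from nonhealth-related fields", organised so that "Four groups of 10 evaluators each will be formed, ensuring diversity in gender and age". They score each image on a five-point scale on which 1 is the feminine end. On allocation the article states: "Each group will be randomly assigned a set of photographs, including preoperative, postoperative, and control images, all displayed in a randomized sequence". It adds, as a safeguard, that "pre- and postoperative images of the same patient will not be included within the same group to minimize direct comparative bias".

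Under Data Analysis for the Cohort Study, the stated method is: "Pre- and postoperative comparisons of continuous variables will be made using paired *t* tests or Wilcoxon signed-rank tests, as appropriate". The same section uses linear regression to relate cephalometric and photometric changes to perceived femininity scores. Neither analysis is described with a rater or rater-group term. The article does not say that pre and post images are balanced within each group, or that the control images are the same in all four sets.

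**The concern.** A paired analysis removes whatever the two measurements share. Here they share the patient but not the raters. Write the change for patient i as

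d_i = true change_i + u(group that rated post) − u(group that rated pre) + rating error,

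where u is the mean severity of a group of 10 students. The separation rule means the two u terms never cancel within a patient. The named tests leave them in the error and, if pre and post were unevenly spread over the groups, would leave part of them in the mean change.

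Perception of femininity is one of three domains of the cohort, and its association with morphological change is a stated aim. With 30 women, the Discussion already concedes limited power for subtle associations, so avoidable noise in this outcome matters.

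**Working it through.** **The plan's own figure.** The rater design has no sample-size or precision figure to reproduce. The only computed figure is the cohort of 30, based on 70 women in the programme, 95% confidence and a 12% margin. With p = 0.5 assumed, n0 = 1.96² × 0.25 / 0.12² = 66.7. The finite-population correction gives 66.7 / (1 + 65.7/70) = 34.4, so 35 rather than 30. That is a separate matter; 30 is used below as stated.

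**Inputs from the article.** 30 patients; four groups of 10 raters; pre and post always in different groups; paired test; significance at 0.05. Two-sided tests are used here. The abstract mentions one-tailed *t* tests, and the Methods do not state sidedness.

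**Assumed inputs.** The article gives no rater variability. Rater severity SD is set at 0.3, 0.5 and 0.8 scale points. The SD of true change is 0.6, with no further rating error.

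**Step 1, size of the group term.** The SD of u is rater SD/√10, so the difference between two groups has SD = rater SD × √(2/10) = 0.13, 0.22 and 0.36 points.

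**Step 2, effect on the standard error.** When the term averages out of the mean, the SE is inflated by about √(1 + 2σ_u²/0.36), where σ_u² = rater SD²/10. This gives 1.02, 1.07 and 1.16. Adding a rater-by-image residual SD of 0.8 raises the other variance to 0.36 + 2 × 0.64/10 = 0.488, and the inflation becomes 1.02, 1.05 and 1.12.

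**Step 3, simulated paired *t* test, 30 differences.** Ranges cover separate simulation runs and slightly different layouts.

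| Allocation | Rater SD 0.3 | 0.5 | 0.8 |
|---|---|---|---|
| Type I error, images placed individually at random | about 5% | about 5% | about 5% |
| Type I error, balanced sets | 4.4% | 3.8–4.4% | 2.8–3.4% |
| Type I error, 80/20 split of pre and post | 7–8% | 11–12% | 18–19% |
| Power for 0.3 points, balanced, no group term | 0.74–0.75 | 0.71 | 0.63–0.64 |
| Power for 0.3 points, balanced, with group term | 0.75–0.77 | 0.75–0.77 | 0.75–0.77 |

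With no group noise at all, power is 0.75. The group term therefore recovers essentially all of the loss, and type I error returns to about 5%.

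**Step 4, sensitivity to the assumptions.** Take instead a true-change SD of 0.3, a rater-by-image residual SD of 0.8 and a change of 0.25 points. Power is 0.80 to 0.82 if the same raters saw both images. It is 0.78, 0.74 and 0.65 with balanced sets rated by different groups. Type I error is 5.0% to 5.6% under individual random placement and 5.6% to 6.5% with mildly uneven sets (pre counts 10, 10, 5, 5). It is 11%, 19% and 32% with strongly uneven sets (13, 13, 2, 2).

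**Step 5, how likely strong imbalance is.** If each pre image is equally likely to fall in either of two pairs of groups, the chance that a given pair holds at least 24 or at most 6 of the 30 is P(X ≤ 6) + P(X ≥ 24), with X ~ Bin(30, 0.5). This is about 0.14%.

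**The case against.** The separation is a deliberate trade-off: it prevents raters from comparing a woman's two photographs directly, and that benefit is real. Random assignment with a mix of image types in each set makes gross imbalance unlikely. Groups are diversified by gender and age, and every set contains controls. Under random or balanced placement the paired test's own standard error already reflects the extra variance. The paired-test sentence covers continuous variables in general, and the article does not say how ten ratings become one score. An allocation list or rater model could sit in a fuller plan that is not shown. The cohort is described as exploratory.

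Most of this stands, and it rules out a stronger reading. A reader might infer that the paired test has a badly inflated false-positive rate, or that the apparent effect of surgery is partly a rater-group artefact. Rates of roughly 24% to 39% (rater SD 0.5 and 0.8, SD of change 0.6) need all pre images in two groups and all post images in the other two. The article excludes this, because each set is to include both kinds. An 80/20 split is compatible with the text but very improbable if images are placed individually at random. It becomes plausible only if uneven sets are built first and then assigned to groups, which the article does not describe.

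What does not fall away is the mismatch between two things the article does state: a rule that puts different raters on the two halves of each pair, and analyses with no term for raters. Diversity in age and gender does not equalise severity between groups of 10, and controls calibrate the groups only if they are shared and used in the analysis.

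**Conclusion.** The point holds as a loss of precision, not as a demonstrated bias. Each third-party change carries a group-severity difference with SD 0.13 to 0.36 points under the assumed rater SDs. With individually random or balanced allocation, the type I error of the paired test is about 5% or lower. At balanced allocation the avoidable loss of power for a 0.3-point change is negligible at rater SD 0.3, about 0.05 at 0.5 and about 0.12 at 0.8. The same noise enters the regression outcome and makes those associations less precise.

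Inflation to about 8% to 19% is conditional on an 80/20 imbalance that the text neither states nor prevents. All these sizes rest on assumed rater and change SDs. This is a cheap improvement, not a must-fix.

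**What to change.** - **Allocation.** Keep the separation rule. Pair the groups (A with B, C with D). For half of each pair's patients show pre in one group and post in the other, and reverse this for the other half. With 30 patients, 16 in A–B (8 and 8) and 14 in C–D (7 and 7) give every group equal numbers of pre and post images.
- **Anchors.** Show the same cisgender control images in all four groups, so that severity can be compared directly and the adjustment survives loss of some post images to attrition.
- **Analysis.** Replace the paired test for third-party ratings with a linear or ordinal mixed model on the individual ratings. Use fixed effects for time and rater group and crossed random effects for patient and rater. Include a random patient-by-time term, so that ten ratings of one photograph are not treated as independent evidence about the change.
- **Regressions.** Use group-adjusted femininity scores.

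The cost is a fixed allocation list, a somewhat more complex model and a few more control images per rater; no extra raters are needed. Postoperative photographs are taken at least 12 months after surgeries planned for 2026, so the allocation can still be set before paired rating begins. If pre and post were left closely aligned with group, no later model could separate surgery from rater severity well.

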###### Cephalometric and Photometric Analysis

Facial morphological changes will be measured pre- and postoperatively using CBCT, an imaging software, and extraoral pictures taken in a frontal and lateral view. The following parameters will be assessed: forehead inclination, true vertical distance, nasofrontal angle, mandibular angle, mandibular plane angle, facial profile, nasolabial angle, mentolabial angle, and mentocervical angle.

##### Data Analysis for the Cohort Study

Descriptive statistics will be used to summarize sociodemographic variables (absolute and relative frequencies). The Shapiro-Wilk test will assess the distribution of continuous variables. Normally distributed variables will be reported as mean and SD; nonnormally distributed variables will be reported as median and IQR. Pre- and postoperative comparisons of continuous variables will be made using paired *t* tests or Wilcoxon signed-rank tests, as appropriate. Categorical variables will be compared using Pearson chi-square or Fisher exact test. Linear regression models will evaluate the associations between cephalometric and photometric changes and perceived femininity scores. Statistical significance will be set at *P*≤.05. All analyses will be conducted using Stata (version 11; StataCorp).

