**Methods:**

The study will include 2 methodological phases: a cross-sectional validation study and a longitudinal cohort study. Phase 1 involves questionnaire development and validation, following the COSMIN (Consensus-Based Standards for the Selection of Health Measurement Instruments) guidelines, with a systematic literature review conducted according to the PRISMA (Preferred Reporting Items for Systematic Reviews and Meta-Analyses) guidelines, expert panel content validation, pilot testing, and psychometric evaluation in a cohort of ≥200 transgender women. Phase 2 is a longitudinal cohort study conducted at San Juan de Dios Hospital in Santiago, Chile, following the STROBE (Strengthening the Reporting of Observational Studies in Epidemiology) guidelines. Thirty transgender women scheduled for facial feminization surgery will be assessed at baseline and 12 months postoperatively. Outcomes include quality of life, self-perceived and third-party–rated femininity, and cephalometric and photometric changes (using cone beam computed tomography). Data analyses include exploratory and confirmatory factor analyses, Cronbach α, paired 1-tailed *t* tests or Wilcoxon signed-rank tests, chi-square or Fisher tests, and linear regression models.

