### Objectives of the Study

This study aims to develop and validate a culturally and linguistically appropriate quality-of-life questionnaire specifically tailored to the transgender population in Chile. It also seeks to evaluate the impact of facial feminization surgery through the analysis of changes in cephalometric and photometric parameters and their association with perceived femininity, as assessed both by third-party evaluators and the participants themselves.

This study hypothesizes that transgender women undergoing facial feminization surgery will experience measurable improvements in quality of life, particularly when facial parameters align more closely with female anatomical standards. In addition, variables such as social participation, employment status, self-perception, and psychosocial stress will be examined to provide a comprehensive understanding of the effects of facial feminization surgery. By integrating multidimensional assessments of psychological well-being, facial morphology, and gender perception, the study aims to generate evidence to inform clinical decision-making and support the development of inclusive, evidence-based health care policies for transgender individuals.

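### Chi-square and Fisher tests are fixed for categorical variables in a one-group before-and-after cohort, so within-woman change would most likely be tested as if the two times were independent groups

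*Protocol article*

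**What the plan says.** The Abstract (Methods) describes a single surgical cohort seen twice: "Thirty transgender women scheduled for facial feminization surgery will be assessed at baseline and 12 months postoperatively". The section Quality of Life Assessment confirms that the same women answer both times: "Participants in the cohort study will complete the validated quality-of-life questionnaire before surgery and again at 12 months postoperatively".

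The section Data Analysis for the Cohort Study recognises the pairing for one type of variable: "Pre- and postoperative comparisons of continuous variables will be made using paired *t* tests or Wilcoxon signed-rank tests, as appropriate". The next sentence is "Categorical variables will be compared using Pearson chi-square or Fisher exact test". The threshold is "Statistical significance will be set at *P*≤.05". The Abstract gives the same set: "paired 1-tailed *t* tests or Wilcoxon signed-rank tests, chi-square or Fisher tests". Neither place names a test for paired categorical data.

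Objectives of the Study says that "variables such as social participation, employment status, self-perception, and psychosocial stress will be examined" to understand the effects of surgery. It gives no scale of measurement for any of them. The only other comparison group is in Femininity Perception Assessment: "A control group of cisgender women will be included, using anonymized clinical photographs".

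**The concern.** Pearson's chi-square and Fisher's exact test assume that the two rows of the table hold different people. In a table of time by category, the 30 women would be counted as 60 independent observations. The information on change lies in the women whose category differs between the two times, and these tests do not use it.

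A woman's employment status before surgery and a year later will usually be positively correlated. In that case the unpaired tests overstate the variance of the change and miss real change more often than a paired test would. The section Anticipated Findings already concedes limited power at n = 30, so this would be an avoidable further loss.

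**Working it through.** **Inputs from the protocol.** n = 30 women, two time points, significance at P≤.05. The protocol gives no effect size, power or within-woman correlation for any categorical variable, so there is no figure on this point to reproduce. The 30 is taken as stated. Its own derivation (population 70, 95% confidence, margin 12%) gives 1.96² × 0.25 / 0.12² = 66.69 and 66.69 / (1 + 65.69/70) = 34.4 if p = 0.5 is assumed, not 30. That is a separate matter and does not affect what follows.

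**Assumptions.** Binary variable; within-woman correlation phi from 0 to 0.6; proportions as shown; two-sided tests. The Abstract says 1-tailed, but only for the t tests.

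**Why the unpaired tests are conservative.** The variance of the change in proportion is [p1(1−p1) + p2(1−p2) − 2·phi·√(p1(1−p1)p2(1−p2))] / n. Unpaired tests omit the last term. With p1 = p2 = 0.5 and phi = 0.5 the true variance is (0.25 + 0.25 − 0.25)/30 = 0.25/30, but the test uses 0.50/30. Its statistic is shrunk by √0.5 = 0.71, so the effective cut-off is 1.96/0.71 ≈ 2.77 and the approximate type I error is 0.006.

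**Exact enumeration.** All outcomes of the paired 2×2 table with 30 women were summed, with cell probability p11 = p1·p2 + phi·√(p1(1−p1)p2(1−p2)). Chi-square has no continuity correction.

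True type I error, 50% at both times:

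| phi | Chi-square | Fisher | Exact McNemar | Asymptotic McNemar |
|---|---|---|---|---|
| 0 | 0.0519 | 0.0274 | 0.0278 | 0.0475 |
| 0.3 | 0.0202 | 0.0085 | 0.0229 | 0.0425 |
| 0.5 | 0.0063 | 0.0020 | 0.0176 | 0.0449 |

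Power for 40% before and 60% after. For example, at phi 0.5, p11 = 0.24 + 0.5 × 0.24 = 0.36, so 0.60 − 0.36 = 24% gain and 0.40 − 0.36 = 4% lose:

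| phi | Gain / lose | Chi-square | Fisher | Exact McNemar | Asymptotic McNemar |
|---|---|---|---|---|---|
| 0 | 36% / 16% | 35.0% | 25.7% | 25.1% | 32.8% |
| 0.3 | 28.8% / 8.8% | 31.9% | 21.6% | 32.5% | 41.9% |
| 0.5 | 24% / 4% | 28.5% | 17.6% | 43.0% | 56.9% |
| 0.6 | 21.6% / 1.6% | 26.1% | 15.0% | 50.8% | 71.6% |

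Other proportions at phi 0.5 (chi-square / Fisher / exact McNemar): 30% to 50% gives 29.1 / 18.2 / 44.3%; 40% to 65% gives 49.5 / 35.0 / 67.4%.

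**Two single tables.**
- 12 of 30 before, 18 of 30 after, 6 gain and none lose. Exact McNemar: 2 × 0.5⁶ = 0.031. Chi-square: 60 × (12×12 − 18×18)² / 30⁴ = 2.4, P = 0.12. Fisher: P = 0.20.
- 13 of 30 before, 20 of 30 after, 8 gain and 1 loses. Exact McNemar P = 0.039, chi-square P = 0.069, Fisher P = 0.12.

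In both, the conclusion at .05 depends on the test. The first, with all change in one direction, is an extreme case.

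**The case against.** **The sentence does not say before and after.** Only the preceding sentence does, and it is limited to continuous variables. Chi-square or Fisher would be apt for comparing different persons, such as the cohort with the cisgender controls. This stands in part: the pre/post reading is an inference. It is a strong one, because the sentence follows directly on the pre/post one, the surgical cohort has one group, sociodemographic variables are assigned to descriptive summary, and the control photographs serve only the third-party ratings. If only between-person comparisons were meant, the rule still needs that restriction.

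**No categorical before-and-after outcome is named.** The three primary domains are quality of life, femininity perception, and cephalometric and photometric change. The morphological parameters are mainly angles. Femininity scores enter a linear regression, so they are treated as numeric. This stands: no primary domain is shown to be affected. Employment status is the clearest candidate, and it is one of several further variables to be examined.

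**The power loss depends on the correlation.** This stands. At phi 0 chi-square has more power than exact McNemar, and at phi 0.3 the two are level. Exact McNemar is itself conservative; the asymptotic form keeps its size closer to 0.05.

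**An article may leave detail to a fuller plan.** True, but here a test is positively stated, in two places, and does not suit the design. That is not an omission.

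**A stronger reading to set aside.** A reader might infer that chi-square will be run on the before-by-after cross-table and its association taken for change, which could give false positives. Nothing in the document suggests this.

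**Conclusion.** The point holds, at the level of something that should be fixed. As written, the plan most likely applies independent-group tests to within-woman change in categorical variables. At an assumed phi of 0.5, power for 40% to 60% is 29% (chi-square) or 18% (Fisher) against 43% for exact McNemar, with true type I error of 0.006 and 0.002. The advantage of exact McNemar over chi-square disappears at phi of about 0.3 and below. These figures rest on assumed proportions and correlations and on two-sided testing.

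A reader might conclude that the study's main results are compromised or that false claims of benefit would follow. The document supports neither. The variables concerned appear to be secondary, in a cohort described as exploratory, and with positive correlation the error is towards missing change.

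**What to change.** Replace the categorical sentence in Data Analysis for the Cohort Study so that it says which comparisons are within the same woman and which are between different persons. For within-woman comparisons, name:
- McNemar's test for binary variables, stating whether exact, mid-p or asymptotic. The exact form is the most cautious of these; the asymptotic form had more power and kept its size below 0.05 in the scenarios above.
- The Stuart-Maxwell test of marginal homogeneity for nominal variables with more than two levels.
- The Wilcoxon signed-rank test for ordered variables. It is already in the plan, but only for continuous ones.

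Keep Pearson chi-square and Fisher for comparisons between independent persons. State whether the categorical tests are two-sided, since the Abstract mentions one tail for the t tests only.

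The cost is one or two sentences. No data, visits or sample size change. Surgeries are planned through 2026 with the second questionnaire 12 months later, so the change can be made before any postoperative outcome is seen, and the test is then not chosen after the fact.
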